### Sample size

Predicting POPC for the clinician is difficult on a case-by-case basis. Therefore, several scoring systems have been developed in the past. The most common of these, the ARISCAT score, has an AUROC of 0.83 [15]. It should be noted that the current literature does not provide any further metrics such as area under the precision-recall curve (AUPRC) or F1 score on the ARISCAT [15,16]. We therefore used the AUROC as the reference metric. The model we aim to create should be significantly better than the ARISCAT score and thus have at least an AUROC of 0.93. Achieving this seems realistic since, in the preliminary work of our research group, prediction models for various postoperative complications have already been created, whose predictive accuracy is in this range [17,18]. With a significance level of 0.05 and a power of 80%, 512 patients would be needed to create the database based on the method described by Hanley and McNeil for comparing ROC curves [19].

Patients are stratified according to the risk criteria determined by ARISCAT so that approximately equal numbers of patients are included in each of the low-risk (ARISCAT < 26 points), intermediate-risk (ARISCAT 26–44 points), and high-risk (ARISCAT ≥ 45 points) groups.

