## Introduction

The incidence of postoperative pulmonary complications (POPC) varies between 9–40%, depending on the surgical procedure and the definition used [1]. Therefore, the introduction of a standardised definition of the outcome “postoperative pulmonary complications”, developed by the Standardised Endpoints for Perioperative Medicine (StEP) collaboration in 2018, represents a prerequisite for future studies in this field [1]. Even supposedly minor complications have the potential to significantly increase the length of hospital stay [2]. Various preoperative risk factors are known but usually cannot be modified. As POPC are the main cause of postoperative morbidity and mortality and the reduction of perioperative mortality is dependent on early recognition and treatment [3], accurate prediction is of paramount interest. There are only a few clinical scoring systems [4]; the currently best-evaluated preoperative score for predicting postoperative pulmonary complications (ARISCAT: Assess Respiratory Risk in Surgical Patients in Catalonia, Table 1) has sufficient sensitivity but lacks specificity [5]. A first retrospective study using machine-learning (ML) methods for determining risk for pneumonia and pulmonary embolism using pre- and intraoperative routine data has shown good accuracy [6]. However, the study shows high specificity but low sensitivity, which could result in overtreatment in clinical practice. In our study, we aim to create a high precision decision-supporting tool for perioperative physicians to identify high-risk patients at an early stage.

**Table 1 pone.0329076.t001:** ARISCAT score.

Score parameters	components	Risk score
Age	≤ 50 years	0
	51-80 years	3
	> 80 years	16
Preoperative oxygen saturation	≥ 96%	0
	91-95%	8
	≤ 90%	24
Respiratory infection in past 1 month	No	0
	Yes	17
Preoperative hemoglobin ≤ 10 mg/dl	No	0
	Yes	11
Incision	Peripheral incision	0
	Upper abdominal incision	15
	Intrathoracic incision	24
Surgery duration	<2h	0
	2-3h	16
	> 3h	23
Emergency procedure	No	0
	Yes	8
**ARISCAT Score**	**Risk**	**Total**
	Low Risk	< 26
	Intermediate Risk	26-44
	High Risk	≥ 45

The table was adapted from [5]; The article was published under the Creative Commons Attribution (CC BY 4.0) license (https://creativecommons.org/licenses/by/4.0/). ARISCAT = Assess Respiratory Risk in Surgical Patients in Catalonia.

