### Model training and evaluation

The primary model development will be based on a dataset of 512 patients. Within this cohort, we will implement stratified k-fold cross-validation (typically 5- or 10-fold, depending on the final class distribution) where possible to assess model robustness and mitigate overfitting. Image-based deep learning models require extensive computational resources, therefore, cross-validation will be applied more selectively. We will therefore use a fixed training/validation/test split for imaging data, ensuring non-overlapping patient groups. Early model experiments will be conducted using internal validation on the training data with hold-out validation to optimize architecture and hyperparameters. Final model evaluation will be performed on an independent hold-out test set.

This hold-out test set will be compiled prospectively during the course of the study after model development, using newly enrolled patients not included in the training dataset. This temporal separation will ensure unbiased performance evaluation of the final model.

Model performance will be evaluated on the independent hold-out test set using several complementary performance metrics. These will include the area under the receiver operating characteristic curve (AUROC), the area under the precision-recall curve (AUPRC), overall accuracy, sensitivity, specificity, F1-score, as well as positive and negative predictive values. Calibration will be assessed using appropriate measures, such as the Brier score, Hosmer-Lemeshaw-Test and calibration curves. Clinical decision-making utility can additionally be evaluated using decision curve analysis (DCA).

Importantly, our models are designed to output individualized risk probabilities, not dichotomous predictions. As such, the selection of a cut-off point for potential clinical decision-making will be a post-modelling step, and risk thresholds for high-risk patient classification will not be predefined. Instead, various thresholding strategies will be explored post hoc, including Youden’s index (for balanced sensitivity and specificity), cut-offs optimized for specific clinical priorities (e.g., maximizing sensitivity), and thresholds guided by DCA.

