### Addressing overfitting and class imbalance

Overfitting will be addressed through the implementation of several regularization techniques commonly used in deep learning. These include dropout layers within the network architecture, L2 weight regularization to penalize large weights, and data augmentation techniques applied to ultrasound images (e.g., rotation, flipping, and zooming). Model complexity will also be restricted as needed.

To better estimate the prevalence and clinical relevance of POPC, we conducted a preliminary single-center observational study involving 259 patients undergoing surgery under general anesthesia. The cohort included 106 female patients (41%) and 62 current smokers (24%) with a median age of 66 years. Overall, 111 patients (43%) experienced at least one POPC, indicating that POPC is a relatively frequent complication in the targeted patient population [25].

Based on this preliminary observational data, only moderate class imbalance is to be expected. Nevertheless, additional strategies will be employed to ensure balanced learning. These include maintaining class ratios across cross-validation folds, monitoring class-wise performance metrics, and using class weighting techniques if imbalances are observed in specific subgroups.

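### The 80% power is attached to 512 database patients, not to the set on which the model is compared with ARISCAT, and that set has no stated size and three conflicting definitions

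*Protocol article*

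**What the plan says.** **Sample size.** The comparator is ARISCAT: "The most common of these, the ARISCAT score, has an AUROC of 0.83". The new model should "have at least an AUROC of 0.93". The calculation is "based on the method described by Hanley and McNeil for comparing ROC curves", and it concludes: "With a significance level of 0.05 and a power of 80%, 512 patients would be needed to create the database". The section prints no event rate, no correlation between the two areas and no sidedness.

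**Event rate.** The section on overfitting and class imbalance reports, from a preliminary cohort of 259 patients: "Overall, 111 patients (43%) experienced at least one POPC". The Introduction says that incidence "varies between 9–40%, depending on the surgical procedure and the definition used".

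**What the 512 are.** Under Trial design they are the total enrolment. Under Model training and evaluation they are the dataset for primary model development.

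**Where the model is judged.** Model training and evaluation says: "Model performance will be evaluated on the independent hold-out test set using several complementary performance metrics". The article describes the evaluation data in three ways:
- The section on the three predictive models divides the dataset into training and hold-out parts.
- Model training and evaluation compiles the hold-out set from patients enrolled after model development and outside the training data.
- The modelling text under Adverse events and harms develops the model on the whole dataset, assesses it by cross-validation, and adds a temporally separate validation set.

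No size is given for any of these.

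**Recruitment.** Trial status gives a first recruitment day of 25/04/2023, an issue date of 21/07/2025, 150 included patients, and completion around 12/2025.

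**The concern.** The power of a comparison of two ROC areas depends on the number of events and non-events among the patients in whom both areas are estimated. Patients used only to train the model add nothing to it. The main hypothesis is that the algorithm outperforms common clinical scores, and ARISCAT is the score on which the sample size rests. The stated 80% should therefore be a property of the patients on whom that comparison is made. In the article it belongs to the database.

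If the hold-out set turns out small, a non-significant difference from ARISCAT could be reported under an 80% power claim that did not apply to it. If all 512 are evaluated, power is far above 80%. Either way, the division between training and testing has not been planned from the power calculation.

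**Working it through.** **Inputs.** From the documents: areas 0.83 and 0.93 (difference 0.10), alpha 0.05, power 80%, Hanley–McNeil method; event rate 111/259 = 43%, or 9–40% from the Introduction. Assumed here because the article gives none: two-sided test, correlation r between the areas of 0 to 0.5, hold-out fractions of 20% and 30%. A paired layout is used because every patient is to have an ARISCAT score.

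**Formulas.** With n1 events and n0 non-events, Q1 = A/(2−A) and Q2 = 2A²/(1+A):

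Var(A) = [A(1−A) + (n1−1)(Q1−A²) + (n0−1)(Q2−A²)] / (n1·n0)

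SE1 = √(V1 + V2 − 2r√(V1·V2)), with V1 at 0.83 and V2 at 0.93.

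Power = Φ[(0.10 − 1.96·SE0)/SE1]. In the alternative-variance form SE0 = SE1. In the null-variance form both areas are 0.83, so SE0 = √(2·V1·(1−r)).

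**Step 1: trying to reproduce 512.** The printed inputs do not fix a single number. At 43% events, 80% power needs:

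| r | Alternative variance | Null variance |
|---|---|---|
| 0 | 210 | 266 |
| 0.3 | 153 | 188 |
| 0.5 | 114 | 137 |

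None is near 512. Other two-sided settings come close: 15% events with r = 0 gives 523, 11% with r = 0.3 gives 507, and 8% with r = 0.5 gives 510 (all alternative variance). With null variance, 20% events and r = 0 gives 498. So 512 corresponds to roughly 8–20% events, with inputs that the article does not print.

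**Step 2: power on the patients evaluated, at 43% events.** Worked example for 20% of 512 = 102 patients: n1 = 43.9, n0 = 58.1, V1 = 0.001834, V2 = 0.000800.
- r = 0, alternative variance: SE1 = 0.0513; Φ[(0.10 − 1.96×0.0513)/0.0513] = Φ(−0.01) = 50%.
- r = 0, null variance: SE0 = 0.0606; Φ[(0.10 − 1.96×0.0606)/0.0513] = Φ(−0.36) = 36%.
- r = 0.5, alternative variance: SE1 = 0.0377; Φ(0.69) = 76%.
- r = 0.5, null variance: SE0 = 0.0428; Φ(0.43) = 66%.

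| Evaluated patients | Alternative variance, r = 0 to 0.5 | Null variance, r = 0 to 0.5 |
|---|---|---|
| 102 (20%) | 50–76% | 36–66% |
| 154 (30%) | 67–90% | 53–85% |
| 512 (all) | at least 99% | at least 98% |

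At 20% events, 102 patients give 29–49% (alternative variance) or 19–39% (null variance). For a separately enrolled hold-out set no power can be computed, because no number is given.

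**Step 3: accrual.** Trial status does not date the count of 150. If it was taken at the issue date, 25/04/2023 to 21/07/2025 is 818 days or 26.9 months, and 150/26.9 = 5.6 per month. The 163 days to 31/12/2025 add 150×163/818 ≈ 30, so about 180 in total. The remaining 512 − 150 = 362 would need about 68 per month over 5.4 months.

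**The case against.** A reader might infer that 512 is an arithmetic error. The documents do not support that. The 43% comes from a preliminary cohort and is cited for class imbalance, not as an input to the sample size. The risk mix of that cohort is not given, and the study recruits the three ARISCAT groups in about equal numbers. Event rates within the Introduction's own range bring the calculation close to 512. Two independent samples at 43% with null variance would need 2×266 = 532, also not far off. The missing inputs may be in the analysis plan (S3 File), which is not shown, so their absence from the article is not in itself a fault. If 43% is right and all 512 are evaluated, the figure is conservative.

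A reader might also infer that the trial is underpowered. That is not shown either. The 20% and 30% fractions are assumptions, the 30% range lies on both sides of 80%, and evaluation of all 512 would give at least 98%.

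Finally, the accrual point says nothing about the power formula and depends on when the 150 were counted.

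All of this stands, and it limits the point to its core. It does not remove the core: the article's sections disagree about what the 512 are and which patients are tested, and an undisclosed event rate would not settle that.

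**Conclusion.** The concern holds in a limited form. The 80% power is a statement about 512 patients in the database, and the article does not tie it to the set on which superiority over ARISCAT is judged. Depending on which description governs, power at 43% events ranges from 36–76% (assumed 20% hold-out) through 53–90% (assumed 30%) to at least 98% (all 512), or is unknown (newly enrolled patients). These figures rest on a two-sided test, a paired layout and r between 0 and 0.5, and they cover both variance forms.

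That 512 cannot be reproduced at 43% events (114–266 needed) is secondary: it shows that the inputs need stating, not that the number is wrong. The recruitment figures are a separate inconsistency, conditional on the date of the count.

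**What to change.** 1. Reconcile Trial design, the section on the three predictive models, Model training and evaluation, and the modelling text under Adverse events and harms. Name one evaluation set, state its size, and say whether it lies inside or outside the 512. Do this before the set is opened.
2. Restate Sample size with the event rate (43%, plus a lower value as sensitivity), the correlation between the areas, the sidedness and the variance form.
3. Attach the resulting power to the named set. If the set is small, state the lower figure. No single test-set size can be prescribed from the article: at 43% events, 80% power needs 153 (r = 0.3) to 210 (r = 0) with alternative variance, but 188 to 266 with null variance.
4. Separately, date the count of 150 in Trial status. If it was taken at the issue date, correct the completion date, or restate the achievable number and its power.

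The cost is recalculation and wording. If the test set is drawn from the 512, no extra patients are needed but fewer remain for training. If it is newly enrolled, it comes on top of the 512 and recruitment must allow for it. The stated power may become less favourable.

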### Outcomes

The primary outcome of the PEPPERMINT study to be predicted by the machine learning model is the risk of developing postoperative pulmonary complications after surgery in general anaesthesia between postoperative days 1 and 7. POPC will be defined and graded by severity according to the standardised criteria of the StEP collaboration [1]. Complications not further described by the StEP collaboration will be defined as from the EPCO (European Perioperative Clinical Outcome) task force [20] as listed in Table 2. POPC, as a composite outcome, summarises atelectasis, pneumonia, acute respiratory distress syndrome (ARDS), pulmonary aspiration, pulmonary embolism, pleural effusion, pneumothorax, and bronchospasm [1]. POPC is assumed as soon as at least one of the listed events occurs and will be detected during the postoperative visit or chart review after the patient is discharged.

**Table 2 pone.0329076.t002:** Definition of postoperative pulmonary complications.

POPC	Definition/Diagnostic	Severity
Atelectasis	Detected on computed tomography OR chest radiography [1]	Mild: therapeutic supplemental oxygen <0.6 FiO_2_ Moderate: therapeutic supplemental oxygen ≥0.6 FiO_2_, requirement for high-flow nasal oxygen or both Severe: unplanned non-invasive mechanical ventilation, CPAP or invasive mechanical ventilation requiring tracheal intubation None: planned use of supplemental oxygen or mechanical respiratory support as part of routine care, but not in response to a complication or deteriorating physiology. Therapies which are purely preventive or prophylactic for example, high flow nasal oxygen or CPAP should be recorded as none
Pneumonia	US Centers for Disease Control Criteria: Two or more serial chest radiographs with at least one of the following (one radiograph is sufficient for patients with no underlying pulmonary or cardiac disease): (i) New or progressive and persistent infiltrates (ii) consolidation (iii) cavitation AND at least one of the following: (a) fever (>38°C) with no other recognized cause (b) leukopenia (white cell count < 4x10^9^ litre-1) or leukocytosis (white cell count > 12x10^9^ litre-1) (c) for adults >70 years old, altered mental status with no other recognized cause AND at least two of the following: (a) new onset of purulent sputum or change in character of sputum, or increased respiratory secretions, or increased suctioning requirements (b) new onset or worsening cough, or dyspnea, or tachypnoea (c) rales or bronchial breath sounds (d) worsening gas exchange (hypoxemia, increased oxygen requirement, increased ventilator demand) [1]	
Acute respiratory distress syndrome	Berlin consensus definition: Timing: within 1 week of a known clinical insult or new or worsening respiratory symptoms AND Chest imaging: bilateral opacities not fully explained by effusions, lobar/lung collapse or nodules AND Origin of edema: respiratory failure not fully explained by cardiac failure or fluid overload (requires objective assessment, e.g., echocardiography, to exclude hydrostatic edema) AND Oxygenation: mild paO_2_:FiO_2_ between 26.7 and 40.0 kPa (200–300 mmHg) with PEEP or CPAP ≥5 cmH2O moderate PaO_2_:FiO_2_ between 13.3 and 26.6 kPa (100–200 mmHg) with PEEP ≥5 cmH2O severe PaO_2_:FiO_2_ ≤ 13.3 kPa (100 mmHg) with PEEP ≥5 cmH2O. OR Mechanical ventilation The need for tracheal re-intubation and mechanical ventilation after extubation, and within 30 days after surgery OR mechanical ventilation for more than 24h after surgery OR Non-invasive ventilation [1]	
Pulmonary aspiration	Clear clinical history (inhalation of regurgitated gastric contents) AND radiological evidence [1,14]	
Respiratory failure	Postoperative PaO_2_ < 8 kPa (60 mmHg) on room air OR a PaO_2_: FiO_2_ < 40 kPa (300 mmHg) OR arterial oxyhemoglobin saturation measured with pulse oximetry < 90% and requiring oxygen therapy [14]	n/a
Pulmonary embolism	Imaging finding (Computed tomography, ventilation/perfusion single photon emission computed tomography, echocardiography)	n/a
Pleural effusion	Chest radiograph with blunting of costophrenic angle, loss of sharp silhouette of the ipsilateral hemidiaphragm in upright position, displacement of adjacent anatomical structures, or (in supine position) hazy opacity in one hemithorax with preserved vascular shadow [14]	n/a
Pneumothorax	Air in the pleural space with no vascular bed surrounding the visceral pleura [14]	n/a
Bronchospasm	Newly detected expiratory wheezing treated with bronchodilators [14]	n/a
Cardiogenic pulmonary edema	Diffuse alveolar interstitial infiltrates with dyspnea and rales related to left ventricular failure, confirmed by echocardiography, pulmonary catheter or clinical improvement with specific treatment [15]	n/a

Postoperative pulmonary complications are defined by the StEP collaboration [1] and complemented by EPCO criteria [20]. Severity is only defined for atelectasis, pneumonia, acute respiratory distress syndrome and aspiration. CPAP = continuous positive airway pressure, FiO_2_ = fraction of inspired oxygen, paO_2 _= partial pressure of arterial oxygen, POPC = Postoperative pulmonary complications.

Outcome assessment will be performed by qualified study staff consisting of three study nurses and two doctoral students on postoperative visits on days 1,3 and 7. To detect complications, visits will include a questionnaire (pulmonary symptoms and mental state), a clinical examination (pulmonary auscultation), the collection of vital parameters (Heart rate, blood pressure, oxygen saturation, breathing rate, temperature) as well as a chart review (oxygen supply, medication, signs of aspiration, admission to ICU). If available during the postoperative course, the following measures will be included: laboratory (c-reactive protein (CRP), procalcitonin (PCT), leukocytes, partial pressure of arterial oxygen (paO_2_), and partial pressure of arterial carbon dioxide (paCO_2_), thoracic imaging (chest radiography or computed tomography) and respiratory support (CPAP, non-invasive or invasive ventilation). All potentially collected parameters are described in Table 3. To check postoperative mental status, the Mini-Cog test will be used. This test consists of a 3-word recall task and the clock drawing test [21].

**Table 3 pone.0329076.t003:** Postoperative visit.

Category	Parameters

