**Escalation of therapy**	
	Admission to PACU or ICU (yes/no)
	NIV (yes/no)
	CPAP (yes/no)
	Intubation (yes/no)
	FiO_2_ [%]
	Antibiotics (free text)
	Dose of antibiotics (free text)
	Bronchodilating medication (free text)
	Dose of bronchodilating medication (free text)

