### Secondary models and endpoints

In addition to the prediction models, we aim to extract specific predictive markers which might be evaluated in an additional study. Once established and evaluated with additional studies, both the AI models and the marker might help to identify high-risk patients, allowing for the adaptation of treatment at an early point of care.

In addition to the primary binary classification model for the presence or absence of POPC, the study will explore the development of additional models that aim to distinguish between different types and severities of complications. These extended models will incorporate more granular outcome definitions, including the timing of complication onset and the presence of multiple complications in a single patient.

Moreover, secondary predictive models will be constructed to estimate outcomes such as quality of postoperative recovery, length of hospital stay, and in-hospital mortality. Important features will be identified based on variable importance metrics. Comparisons between patients with and without complications will be conducted using appropriate statistical tests, including t-tests or Mann-Whitney U tests for continuous variables, and chi-squared or Fisher’s exact tests for categorical variables.

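### The ARDS row of Table 2 counts re-intubation, prolonged ventilation or any non-invasive ventilation without a respiratory cause, so a second anaesthetic or preventive support is labelled POPC

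*Protocol article*

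**What the plan says.** In the Outcomes section of the protocol article, the ARDS row of Table 2 sets out the Berlin definition as four conditions that must all be met: timing, imaging, origin of oedema and oxygenation. The same row then continues with OR and the label Mechanical ventilation, defined first as "The need for tracheal re-intubation and mechanical ventilation after extubation, and within 30 days after surgery". Two further alternatives follow, also joined by OR: mechanical ventilation for more than 24 hours after surgery, and non-invasive ventilation. None of the three carries an imaging, gas-exchange or causal condition.

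The text above the table names ARDS as a component of the composite. It does not list mechanical ventilation or NIV as components. The scoring rule is "POPC is assumed as soon as at least one of the listed events occurs", with no severity threshold. The outcome window is "between postoperative days 1 and 7".

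The severity column has a grade of none. It covers planned oxygen or mechanical support that belongs to routine care and is not a response to a complication, and also purely preventive therapy, with high-flow oxygen and CPAP as examples. The table footnote says severity is defined for ARDS among other events.

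Table 3 records intubation, NIV and CPAP at each visit as yes or no, with no reason. Secondary models and endpoints plans "additional models that aim to distinguish between different types and severities of complications".

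**The concern.** Read as printed, the OR branches are a free-standing route into the primary outcome. A patient extubated after the index operation who returns to theatre under intubated anaesthesia satisfies the first branch, whatever the state of the lungs. A patient given NIV as prevention satisfies the third. The Introduction itself names postoperative NIV as a preventive measure, so this use is foreseeable in the study population.

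The label matters more here than in many studies. Study measures states that the images receive no expert annotation and that POPC is the only label. Patients labelled positive for non-pulmonary reasons are noise that a recovery-room lung scan cannot be expected to predict. Outcomes are assessed by three study nurses and two doctoral students, so the written rule has to settle such cases.

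**Working it through.** **Step 1: trace the rule.**

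- *Does the branch stand alone?* It has its own label (Mechanical ventilation) and its own time limits (30 days, 24 hours), which differ from the Berlin one-week limit. The natural reading is an alternative to the whole Berlin definition.
- *Does it reach the primary outcome?* Yes. It sits in the ARDS row, ARDS is a listed component, and one event suffices.
- *Does another passage remove these patients?* The secondary exclusions in Eligibility criteria cover only discharge or transfer on the day of surgery, cancellation or postponement, and immediate unplanned ICU admission after an intraoperative complication. Modifications, adherence and concomitant care prohibits no intervention and does not stop follow-up at a second operation.
- *Does severity none remove them?* It grades an event. Nothing says that an event graded none is not an event, so a case could be graded none and still count as POPC.
- *Do other rows carry cause conditions?* Yes. The pneumonia row requires fever or altered mental status without another recognised cause, and the cardiogenic oedema row requires a link to left ventricular failure. The ventilation branches have nothing comparable.
- *Do the windows agree?* No. The branch runs to 30 days, the outcome covers days 1 to 7, and follow-up visits end at discharge if that comes earlier.

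**Step 2: size of the re-intubation branch.** The plan states no figure on this point, so there is none to reproduce. Inputs:

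- N = 512 (Sample size).
- p = 111/259 = 0.4286, POPC from other causes (preliminary cohort, Addressing overfitting and class imbalance).
- AUROC 0.93 as target and 0.83 for ARISCAT (Sample size).
- r, the share with a second intubated anaesthetic in hospital on days 1 to 7. The documents do not give it; 1%, 2% and 5% are assumed, independent of POPC.

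Flipped labels = N × r × (1 − p). Positives otherwise = 512 × 0.4286 = 219.4. Share of positives f = flipped / (219.4 + flipped).

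- r = 1%: 512 × 0.01 × 0.5714 = 2.9; f = 2.9/222.4 = 1.3%.
- r = 2%: 512 × 0.02 × 0.5714 = 5.9; f = 5.9/225.3 = 2.6%.
- r = 5%: 512 × 0.05 × 0.5714 = 14.6; f = 14.6/234.1 = 6.25%, about 6.3%.

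**Step 3: effect on AUROC.** Assume that neither score carries information on the flipped patients. Then observed AUROC = (1 − f) × true AUROC + f × 0.5.

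- Model, true 0.93: 0.924, 0.919 and 0.903 at r = 1%, 2% and 5%.
- ARISCAT, true 0.83: 0.826, 0.821 and 0.809.
- Difference = (1 − f) × 0.10: 0.099, 0.097 and 0.094.

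The absolute AUROC falls by 0.006 to 0.027. The planned difference from ARISCAT falls by only 0.001 to 0.006. The NIV branch cannot be sized, because the documents give no rate of preventive NIV.

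**The case against.** Four objections deserve an answer.

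First, the row has no brackets, so OR could replace only the oxygenation criterion. Imaging, timing and oedema conditions would then still apply and the reoperation case would fail. That reading is possible but strained, given the branch's separate label and time limits. If both readings are open, the row still needs repair.

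Second, severity none shows that the plan distinguishes planned or preventive support from support given for a complication. That is fair, and a planned staged operation fits the text well. But the link from grade to event is not written down.

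Third, the row cites the consensus definition, and the wording may be faithful to it. The source is not at hand, so nothing can be said about where the wording came from or what was intended. The printed rule is what assessors will apply.

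Fourth, the size rests on an assumed rate. This stands. A positive association between reoperation and POPC would also mean fewer flipped labels.

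Two stronger readings are tempting. A reader might infer from Table 3 that these cases can never be told apart. The documents do not support this: outcome assessment includes chart review, discharge letters are searched, and perioperative data can be exported from the patient data management system. A reader might also infer that most patients classed as ARDS would be reoperations. That needs rates of reoperation and of true ARDS that the documents do not give. It would also have to count patients entering through respiratory re-intubation, ventilation beyond 24 hours and NIV.

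**Conclusion.** The point holds as a wrongly stated outcome rule. Three passages need to be reconciled with the ARDS row: the list of composite components, the severity grade none, and the day 1 to 7 window.

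The effect on the primary outcome is modest: about 3 to 15 of 512 labels, or 1.3–6.3% of positives, if 1–5% have a second intubated anaesthetic in the window independently of POPC. The AUROC figures also assume scores that are uninformative for these patients. The comparison with ARISCAT is affected much less than the absolute AUROC. Late reoperations should not be added to this count: although the row says 30 days, the stated primary window ends on day 7.

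The exploratory models by complication type would have a contaminated ARDS class, to an extent that cannot be determined from the documents. The change is worth making because it corrects the study's main label at little cost.

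**What to change.** 1. Restrict the ARDS row to the Berlin criteria.
2. Put the re-intubation, prolonged ventilation and NIV clause in a row of its own. State whether it is a component of the composite, and bring it into line with the component list, the severity grade none and the day 1 to 7 window.
3. State, for outcome classification only, that intubation solely for a further procedure and purely preventive support do not count as POPC.
4. Add a reason field for intubation and NIV to Table 3 and to the tablet form.
5. Re-code affected patients already enrolled from charts, discharge letters and the patient data management system.

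The cost is a reworded table, one added form item and limited re-coding. Trial status reports 150 patients included. At the assumed 1–5%, that is 150 × 0.01 = 1.5 to 150 × 0.05 = 7.5 re-intubated patients, plus any who received NIV. Any departure from the cited consensus definition has to be reported, because it reduces comparability with studies that use that definition unchanged.
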